**Figure 2 fig2:**
[figure not shown]
Location of acupoints.

**Table 2 tab2:** Composition and manipulation of acupuncture.

Acupoints	Location	Manipulation
Neiguan (PC6) (bilateral side)	Pericardium meridian; On the anterior aspect of the forearm, between the tendons of the palmaris longus and the flexor carpi radialis, 2 B-cun (50 mm) proximal to the palmar wrist crease.	Perpendicularly insert approximately 0.5 to 1.0 B-cun (13 mm-25 mm) into the skin, applying combinative manipulation (lifting-thrusting and twirling-rotating) with reducing method bilaterally for 1 min.
Shuigou (GV26)	Governor vessel; On the face, at the junction of the upper 1/3 and lower 2/3 of the philtrum midline.	Obliquely insert upwards to the nasal septum for 0.3–0.5 B-cun (8 mm-13 mm) with heavy bird-pecking method until the patient’s eyeballs have moistened or tears flow.
Sanyinjiao (SP6) (affected side)	Spleen meridian; On the tibial aspect of the leg, posterior to the medial border of the tibia, 3B-cun(75 mm)superior to the prominence of the medial malleolus.	Obliquely insert the point edged the posterior tibia by 45° with skin for 1.0–1.5 B-cun (25 mm-40 mm), and apply tonifying method of lifting-thrusting till the affected side lower limb has jerked 3 times.
Baihui (GV20)	Governor vessel; On the head, 5B-cun(125 mm)superior to the anterior hairline, on the anterior median line.	Obliquely insert toward to back of the head 0.3–0.5 B-cun (25 mm–40 mm) with twirling uniform reinforcing-reducing manipulation for 1 min. Retention for 30 min.
Sishencong (EX-HN1)	Extra point; On the head, 1B-cun(25 mm)around the GV20, and composed of 4 acupoints.	Obliquely insert toward to back of the head 0.3–0.5 B-cun (8 mm–13 mm) with twirling uniform reinforcing-reducing manipulation for 1 min. Retention for 30 min
Shangxing (GV23)	Governor vessel; On the head, 1B-cun(25 mm)superior to the anterior hairline, on the anterior median line.	Subcutaneously insert toward to back of the head 1–1.5 B-cun (25 mm–40 mm) with reinforcing manipulation for 1 min. Twirling manipulation should have amplitude of <90 and frequency of 120–160 turns/ min. Retention for 30 min.
Yintang (EX-HN3)	Extra point; On the forehead, at the midpoint of the line between two brows.	Obliquely insert toward to the nasion 0.2–0.3 B-cun (5 mm-8 mm) with light bird-pecking method until the patient’s eyeballs wetting. Retention for 30 min.

Secondly, MRI-navigated rTMS treatment will include three parts. First, all MRI scans will be taken on a 3 T MRI Scanner with a 32-channel head coil (Philips Achieva 3 T ingenia CX Medical Systems, Netherlands). High-resolution T1-weighted anatomical images will be acquired with TR/TE = 9.8/4.6 ms, flip angle = 8°, FOV = 240 × 240 × 192 mm^3^, matrix = 240 × 240, voxel size = 1 mm isotropic. Second, surface electromyography (EMG) will be adopted to record motor evoked potentials (MEPs) from the abductor pollicis brevis (APB) for determining the resting motor threshold (rMT) of the non-lesioned motor cortex hand representation. A single TMS pulse at 0.2 Hz ± 10% will be delivered to the location to identify the rMT. rMT is defined as the minimum stimulus intensity capable of evoking at least five MEPs of more than 50 μV peak-to-peak amplitude in 10 consecutive trials. The stimulation will be delivered using a Y125-round coil (YRD CCY-II, YIRUIDE GROUP, China). Finally, MRI-navigated, targeted rTMS using a BrainSight system and left DLPFC targeting will be individualized by reconstructing MRI data into a 3-dimensional brain image for neuronavigation. Left DLPFC localization will be the central middle frontal gyrus, between the superior frontal sulcus (BA46) and the middle frontal sulcus (BA9), based on T1-weighted anatomical image data. After navigated localization, focal rTMS will be administered using a Magstim Rapid 2 (Magstim, UK) connected to the identical active Y125-round coil. When treating, rTMS will be applied at 110% RMT to the left DLPFC, with 12 to 20 sessions of 10 Hz (4 s on and 26 s off) rTMS, and a total of 3,000 pulses per session administered 37.5 min per day over the 4-week period.

### Control group

Patients in the control group will only be given MRI-navigated rTMS in the same way as the treatment group.

### Prohibited treatments

Drugs, psychotherapy, transcranial electrical stimulation, music therapy, and other treatments for PSD will be prohibited during the study period. Moreover, acupoints for PSD that are not included in the protocol will also be prohibited.

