Acupuncture is a typical, promising, and traditional non-drug therapy, which has been widely used in the treatment of stroke-related diseases in China. Acupuncture, as a national heritage of China, has been recommended for PSD in many international guidelines (11, 12). A network meta-analysis of acupuncture has revealed that, as an adjunctive therapy, it is effective and safety for improving depression in stroke survivors and, combined with repetitive transcranial magnetic stimulation (rTMS), would be a better strategy, with the highest probability (13). The American FDA has approved rTMS as a non-invasive physiotherapy technique, and it is one of the commonly used neuroregulatory techniques for depression in the world. It is reported that publicly funding rTMS for adults with treatment-resistant depression in Ontario over the next 5 years would add $63.2 million in total costs (14). A meta-analysis has shown that patients with PSD may benefit from rTMS (15). Moreover, stroke survivors with depression had positive attitudes toward rTMS (16). rTMS delivers magnetic pulses to stimulate the areas of the brain associated with mood regulation. However, the efficacy of rTMS can be greatly affected by the precise position of the rTMS coil on the scalp (17). In terms of therapeutic target selection, high-frequency rTMS in the left dorso-lateral prefrontal cortex (DLPFC) is often recommended in guidelines to treat PSD (18). However, clinical rTMS typically uses scalp-based landmarks for DLPFC targeting (the ‘5-cm rule’), which cannot achieve accurate positioning because of anatomical differences between individuals. In this study, an alternative method of individual anatomical MRI-guided neuronavigation will be used to accurately locate the DLPFC, so as to realize the focusing and individualization of rTMS targeting. Therefore, acupuncture and rTMS may be a promising choice for PSD.

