### Subjects

#### Recruitment strategies

This study will be carried out at the Nanjing Drum Tower Hospital, The Affiliated Hospital of Nanjing University Medical School. All participants will be recruited from the department of TCM, the department of neurology, or the department of psychology. Three doctors ([name], [name], and [name]) will help to recruit patients and healthy participants from three departments. Recruiting posters and a WeChat platform will be also adopted to collect cases.

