### Drop-out criteria

Low compliance and reluctantly continue to participate in the trial.Unsuitable to continue participation due to serious adverse reactions or complications during the study.Incompliance with standard treatments (less than 50% of The treatment times or receive other unrelated treatments) and/or MRI scanning or incomplete observation data affecting The assessment.

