### Intervention

#### Initial therapy

During the 4-week study period, basic treatments for stroke such as antihypertensive agents, anticoagulants and antiplatelet agents, antidiabetic agents, and lipid-lowering drugs, will be allowed to be routinely received. Complication prevention (pressure ulcers and pneumonia) and nutritional support will also be allowed.

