### Compliance and discontinuation

Based on the above-mentioned withdrawal criteria, if a participant receives more than six EA/rTMS sessions, this will be considered a valid case to generate reliable data. For patients who drop out without enough sessions, their last visit data will be used for result analysis.

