### Blinding

For blinding, because the intervention style will seem dissimilar between EA + rTMS and single rTMS, an open label design will be adopted. However, all subjects will be treated separately to prevent communication in different rooms. Moreover, the MRI scan technicians, outcome assessors, data entry clerks, data administrators, and data statisticians will all be blinded to the grouping with labels A and B.

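### Dropping a patient for receiving an outside treatment can put baseline in place of the week-4 HAMD-24; acupuncture for a non-PSD stroke symptom falls under this rule because it is not expressly barred

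*Protocol article*

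**What the plan says.** All references are to the protocol article.

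- **Prohibited treatments.** Drugs, psychotherapy, transcranial electrical stimulation and music therapy are named, followed by "and other treatments for PSD will be prohibited during the study period". For needling, "acupoints for PSD that are not included in the protocol will also be prohibited". Both limits are tied to the PSD indication.
- **Initial therapy.** Background care is an open list: "basic treatments for stroke such as antihypertensive agents, anticoagulants and antiplatelet agents", with other drugs, prevention of complications and nutritional support. Acupuncture for another symptom is neither listed nor excluded.
- **Drop-out criteria.** Non-compliance is described as "less than 50% of The treatment times or receive other unrelated treatments". The article does not define which treatments count as unrelated.
- **Compliance and discontinuation.** For patients who drop out without enough sessions, "their last visit data will be used for result analysis". A patient with more than six sessions is a valid case.
- **Primary outcomes; Data collection and management; Statistical analysis.** HAMD-24 is scored at baseline and at 4 weeks, there are two visits, and missing endpoints are filled by LOCF under modified intention to treat.
- **Control group.** Controls receive navigated rTMS alone, so EA is the only randomised difference.

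**The concern.** In a trial of EA added to rTMS, acupuncture from outside the trial is the co-treatment that bears most directly on the comparison. The ban is defined by indication, so needling for another stroke complaint is left to a rule that acts only after the event and removes the patient.

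That rule matters because of what follows it. With no visit between baseline and week 4, the only value LOCF can carry forward is baseline. A control who had improved on rTMS would then be analysed as not having improved, which favours EA. An EA patient handled the same way pulls the result in the other direction.

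Exposure is plausible, though not shown. The Introduction says acupuncture "has been widely used in the treatment of stroke-related diseases in China". Under Recruitment strategies, "All participants will be recruited from the department of TCM", neurology or psychology. Under Blinding, "an open label design will be adopted", so controls know that they are not receiving EA.

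**Working it through.** **Inputs (Sample size section).** Baseline HAMD-24, mean (SD): 27.52 (2.06) EA, 27.84 (2.55) control. Week 4: 11.06 (3.37) EA, 14.13 (3.15) control. Two-sided 5%, power 0.90, 1:1 allocation, 20% drop-out, 32 per arm.

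**1. The plan's own figure.** Difference 14.13 - 11.06 = 3.07. Pooled SD = sqrt((3.37² + 3.15²)/2) = 3.26. The two-sample t test needs 25 per arm (power 0.903; 24 per arm gives 0.891). Then 25/0.8 = 31.25, rounded up to 32 per arm and 64 in total. The stated sample size reproduces.

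**2. Shift in the expected difference (control minus EA) per affected patient, at 32 per arm.** The affected patient is taken to be typical of the arm.

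- Control kept with the observed score, assuming outside needling gives the full EA effect (upper bound): -3.07/32 = -0.10.
- Control without a week-4 score, baseline carried forward: (27.84 - 14.13)/32 = 13.71/32 = +0.43.
- EA patient without a week-4 score, baseline carried forward: -(27.52 - 11.06)/32 = -16.46/32 = -0.51.

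The primary outcome is change from baseline, for which the same values imply a difference of 16.46 - 13.71 = 2.75. The two carried-forward shifts are the same on that scale, because the patient's change becomes zero. The upper bound for dilution becomes 2.75/32 = 0.09.

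**3. One, two or three affected patients.** Differences follow from step 2. Power is simulated: 100,000 trials, normal scores, k patients replaced, two-sided 5% t test. With none affected, the difference is 3.07 and power is 0.96.

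| Scenario | Difference, k = 1, 2, 3 | Power, k = 1, 2, 3 |
|---|---|---|
| Controls kept, full EA effect | 2.97, 2.88, 2.78 | 0.95, 0.93, 0.91 |
| Controls only, baseline carried forward | 3.50, 3.93, 4.36 | not meaningful: the difference is inflated |
| EA patients only, baseline carried forward | 2.56, 2.04, 1.53 | 0.79, 0.44, 0.15 |
| k in each arm, baseline carried forward | 2.98, 2.90, 2.81 | 0.86, 0.71, 0.53 |

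One control with baseline carried forward moves the estimate by 0.43/3.07 = 14% of the planned difference. That is more than four times the upper-bound dilution from keeping the same patient (0.428/0.096 = 4.5). When both arms lose equally, the bias nearly cancels but the added spread costs power.

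**4. Larger dilution, as an assumption.** The documents give no rate of outside acupuncture. If 10% or 20% of controls received it with the full EA effect and were kept, the difference would be 2.76 or 2.46. Power would be 0.905 or 0.82 at 32 per arm, and 0.82 or 0.71 if only 25 per arm were analysed.

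**The case against.** **The protocol already treats outside acupuncture as a breach.** Needling for PSD falls under Prohibited treatments, needling for anything else most naturally falls under unrelated treatments in Drop-out criteria, and controls are to receive only rTMS. This stands. A reader might infer that the protocol permits controls to have acupuncture, and the text does not support that. What is missing is an express bar in advance; the rule that does exist works by removing the patient.

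**The larger shift comes from LOCF with two visits, not from the wording of the ban.** This also stands. It would affect any patient without a week-4 score, and widening the ban alone would not remove it. The point is therefore about a drop-out rule that can create avoidable missing scores, with the ban as a second step.

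**Several things must all happen.** Outside needling must occur, be disclosed, be classed as unrelated, lead to withdrawal, and leave no week-4 score. Nothing says that week 4 is skipped after a breach. The last-visit rule under Compliance and discontinuation is worded for patients with too few sessions, and LOCF applies only where the endpoint is missing. So it would be wrong to conclude that every such patient is analysed at baseline. Nor is a contradiction between the two sections claimed.

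**Exposure is inferred, and the full EA effect is generous.** Entry requires NIHSS below 6, and aphasia, peripheral neuropathy and spinal lesions are excluded, which removes some reasons for other needling. Needling for another symptom need not act on depression. Both remarks are fair, which is why 0.10 is given as an upper bound and no rate is asserted.

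**The article is condensed.** A fuller protocol may itemise concomitant care. But the article does state a drop-out rule and the scope of the ban, and it is those stated rules that are questioned here.

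**Conclusion.** The concern holds as a low-cost improvement that should be made. Followed as written, the drop-out rule for unrelated treatments can turn a patient who could have been assessed into one analysed at baseline. The shift is about +0.43 points per control and -0.51 per EA patient on a planned difference of 3.07, at 32 per arm.

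This rests on three assumptions: the planning values apply, the affected patients are typical of their arm, and no week-4 HAMD-24 is taken. If the score is taken, the shift does not arise.

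Two stronger readings are not supported. One is that contamination alone undermines the trial: with one to three controls kept at the full EA effect and 32 per arm analysed, power stays at 0.91 or more. The other is that the bias must favour EA: its direction depends on which arm loses patients, and the documents give neither a rate nor a split by arm.

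**What to change.** 1. **Drop-out criteria:** state that receiving a non-trial treatment does not end follow-up. Replace the undefined reference to unrelated treatments with a reference to those listed under Prohibited treatments.
2. **Assessment and analysis:** still assess HAMD-24 at the scheduled week-4 visit after any breach, and analyse the observed score in the randomised arm. This step removes the larger shift.
3. **Prohibited treatments:** add that during the 4 weeks neither arm receives acupuncture or EA outside trial sessions, for any indication.
4. **Recording:** log breaches by arm on the treatment cards already described under Quality control.

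The cost is a wording amendment and one extra line on the card, with no added visit and no change in sample size. Patients forgo non-trial acupuncture for 4 weeks. If recruitment has ended, analysing the observed score in the randomised arm can still be applied wherever a week-4 score exists.

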### Compliance and discontinuation

Based on the above-mentioned withdrawal criteria, if a participant receives more than six EA/rTMS sessions, this will be considered a valid case to generate reliable data. For patients who drop out without enough sessions, their last visit data will be used for result analysis.

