### Outcome measures

#### Primary outcomes

The first primary outcome will be the clinical efficacy evaluated by the change of the Hamilton Depression Rating Scale (HAMD) with 24 items (HAMD-24), which meet the scoring criteria as follows: a total score of <8 indicates normal, a total score of ≥8 indicates different levels of depressive symptoms, and a higher score indicates more severe depression. As an other-report and screening questionnaire, individuals with depression will be diagnosed using this scale before enrollment. A HAMD-24 score ≥ 8 will be considered as one of the inclusion criteria in this study. The HAMD-24 score will be assessed at baseline and at 4 weeks.

The second primary outcome will be the change of rs-fMRI in probing possible central mechanisms. Functional neuroimages will be collected using a 3.0 Tesla Philips Ingenia CX MRI system in our hospital. Rs-fMRI data will include three-dimensional T1 weighted structural imaging with a FSE sequence and BOLD imaging with a SE-GRE-EPI sequence for 7.5 min, covering the whole brain. The parameters for 3D-T1* imaging will include a slice thickness of 1 mm, a TR/TE of 9.8 ms/4.6 ms, an FOV of 240× 240 × 192 mm^3^, a flip angle of 8^°^, a matrix of 240 × 240, an in-plane resolution of 1 × 1 × 1 mm^3^, and 192 layers. The parameters for BOLD imaging will include a slice thickness of 4 mm, a TR/TE of 2,000 ms/30 ms, a flip angle of 90^°^, a matrix of 64 × 64, an FOV of 192 × 192 × 140 mm^3^, 35 layers, and 320 time points.

The fMRI data will be preprocessed with the DPABI toolkit.^1^ Preprocessing steps will mainly include slice timing, realignment, regression, normalization, smoothing, detrending, and filtering, similar to a previous study (25).

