### Informed consent

The informed consent form has been approved by the Medical Ethics Committee of the Affiliated Drum Tower Hospital, Medical School of Nanjing University (version 1.1). Subjects will be informed of all aspects of the trial, which include the study background and purpose, inclusion and exclusion criteria, available treatments and alternatives, and benefits and harms, as well as rights and duties of the participants. More importantly, informed consent will be obtained from each patient and healthy person before grouping. If patients drop out at any time during the study, the collected data will still be retained for mITT analysis.

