### Data collection and management

During the 4 week clinical study, patients will need to receive EA + rTMS or rTMS alone for 4 consecutive weeks, and two visits will be needed to complete fMRI scans and a series of scales at baseline and at 4 weeks. After screening, the raw data will be comprehensively documented in paper CRF (pCRF) within 2 days and electronic CRF (eCRF) will be completed in the electronic data capture (EDC) system^3^ within 14 days. Nobody, except for the PI ([name]) and clinical research associates (CRA) ([name]) will be eligible to review the database. The raw pCRF documents will be kept in the archives of the Affiliated Drum Tower Hospital, Medical School of Nanjing University for more than 5 years after study completion.

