### Statistical analysis

All data analyses of this study will be done by an independent statistician ([name]) from University of Cape Town in South Africa using IBM SPSS Statistics for Windows, version 25.0 (IBMCorp., Armonk, N.Y., USA). The modified intention to treat (mITT) principle will be applied for all outcomes in the full analysis set. If the endpoints are missing, the last-observation-carried-forward (LOCF) method will be used according to mITT analysis. The mean, standard deviation (SD), minimum (min), maximum (max), and median will be reported for the quantitation data. The frequency (*n*) and corresponding percentage (%) will be given for the enumeration data. For intra-group comparisons, Student’s paired t test or Wilcoxon signed rank test will be used, and the chi-squared test will be utilized for qualitative indexes. For inter-group comparisons, independent-sample T test or Mann–Whitney U test will be applied. Pearson correlation coefficient or Spearman correlation coefficient will be used for correlation analysis between scale scores and fMRI data. An alpha level of 5% (2-tailed) will be selected.

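### HAMD-24 is rated only at baseline and week 4, so carrying the last value forward gives any analysed patient without a week-4 rating a change of exactly zero

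*Protocol article*

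**What the plan says.** The primary clinical outcome is the change in HAMD-24 from baseline to week 4. The Primary outcomes section gives the rating times: "The HAMD-24 score will be assessed at baseline and at 4 weeks". The Data collection and management section agrees: "two visits will be needed to complete fMRI scans and a series of scales at baseline and at 4 weeks". Table 1 has one assessment column after enrolment, at day 28 ± 5. No interim or early-termination rating is described.

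Three sections deal with patients who leave early or lack an endpoint:

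- Compliance and discontinuation: "For patients who drop out without enough sessions, their last visit data will be used for result analysis".
- Statistical analysis: "If the endpoints are missing, the last-observation-carried-forward (LOCF) method will be used according to mITT analysis".
- Informed consent: "If patients drop out at any time during the study, the collected data will still be retained for mITT analysis".

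The Drop-out criteria cover patients with "less than 50% of The treatment times or receive other unrelated treatments", and also those with "incomplete observation data affecting The assessment". The article does not define mITT.

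**The concern.** LOCF needs an earlier on-treatment value to carry. Here the only earlier HAMD-24 value is the one taken before treatment. A patient in the analysis set without a week-4 rating therefore enters with week 4 equal to baseline, which is a change of exactly zero.

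Two things are at stake. First, among changes planned at about 14 to 16 points, a few zeros inflate the SD of change and cost power even when both arms lose the same number. Second, if the arms lose different numbers, the estimated difference moves with the imbalance. The trial is open-label and one arm has an added procedure, so equal loss cannot be taken for granted.

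**Working it through.** **The plan's own figure.** From the Sample size section, the week-4 means (SD) are 11.06 (3.37) and 14.13 (3.15).

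- Difference 14.13 − 11.06 = 3.07. Pooled SD √((3.37² + 3.15²)/2) = 3.26. Standardised effect 3.07/3.26 = 0.94.
- The two-sided 5% t test reaches power 0.903 with 25 per arm (0.891 with 24). Then 25/0.8 = 31.25, rounded up to 32 per arm, 64 in total. The stated size is reproduced and is not in question.

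**Planned changes.** The baseline means (SD) are 27.52 (2.06) and 27.84 (2.55).

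- EA + rTMS: 27.52 − 11.06 = 16.46. rTMS: 27.84 − 14.13 = 13.71. Difference 2.75.
- SD of change = √(s₀² + s₁² − 2·r·s₀·s₁). The correlation r is not in the article. At an assumed r = 0.5 the SDs are 2.94 and 2.90.

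**Three of 32 per arm scored zero** (f = 3/32).

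- Means: 29/32 × 16.46 = 14.92 and 29/32 × 13.71 = 12.42. The difference is 2.49 from unrounded values, 91% of 2.75.
- SDs, from √((1−f)·SD² + f(1−f)·mean²): 5.56 and 4.86.
- Difference over standard error: without zeros 2.75/√((2.94² + 2.90²)/32) = 2.75/0.73 = 3.8. With zeros 2.49/√((5.56² + 4.86²)/32) = 2.49/1.31 = 1.9. Most of the loss comes from the SD.

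**Simulated t-test power on change** (32 per arm, normal changes, 40,000 trials per setting, same number of zeros in each arm):

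| r | 0 zeros | 1 | 3 | 6 |
|---|---|---|---|---|
| 0 | 0.77 | 0.61 | 0.32 | 0.08 |
| 0.3 | 0.89 | 0.74 | 0.37 | 0.07 |
| 0.5 | 0.96 | 0.83 | 0.42 | 0.06 |
| 0.7 | 0.995 | 0.94 | 0.49 | 0.04 |

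Six per arm is roughly the planned 20% drop-out (0.2 × 32 = 6.4), if none of those patients had a week-4 rating. If each patient is instead lost at random with probability 20%, so that the count varies by arm, the approximate power at r = 0.5 is 0.27.

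**Comparisons at r = 0.5.**

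- Mann-Whitney, which the Statistical analysis section also allows: 0.95, 0.93, 0.87 and 0.69 with 0, 1, 3 and 6 zeros per arm.
- Week-4 scores compared instead of changes, with baseline carried forward: t-test power 0.54 with 3 per arm and 0.14 with 6.
- Three or six patients per arm left out at random: t-test power 0.94 or 0.91. The loss therefore comes from the imputed zeros, and the smaller number of patients explains little of it.
- Smaller mean changes of 9.6 and 6.85 (an assumption that keeps the 2.75 difference and the SDs): 0.96, 0.92, 0.82 and 0.57 with 0, 1, 3 and 6 zeros per arm.

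**Unequal loss.** With three zeros among controls only, the expected difference is 16.46 − 12.42 = 4.04. With three in the experimental arm only, it is 14.92 − 13.71 = 1.21. The planned value is 2.75. With no true effect, and zero-scored controls who would have improved by the planned mean, t-test false rejection is about 5%, 8–9% and 13–18% with one, two and three such controls (r from 0 to 0.7). For Mann-Whitney with three it is about 8% at r = 0.5.

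**The case against.** **mITT is undefined.** A definition that requires a post-baseline score would remove these patients, and the inflation from 25 to 32 per arm fits an expectation of about 25 evaluable patients. This stands as an uncertainty. However, under that definition LOCF would have nothing to fill for HAMD-24, and the Compliance and Informed consent sections both point to keeping drop-outs in. The natural reading is that baseline is carried forward.

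**The t test may not be the test used.** The article allows Mann-Whitney and states no rule for choosing. If the choice followed a normality check, one zero among such changes would usually lead to Mann-Whitney, whose loss is much smaller. This stands, and both tests need to be shown.

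**The baseline is borrowed.** Eligibility requires only a HAMD-24 above 8, while the mean of about 27.5 comes from another study. With milder patients the zeros are less extreme and the loss shrinks. This also stands.

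**Readings that go too far.** A reader might infer that every drop-out is scored zero, or that week-4 ratings of patients with few sessions are thrown away. The documents do not say so: a patient who stops treatment but attends on day 28 ± 5 has a real week-4 score, and that score can be the last visit data. A reader might also see a flat contradiction between the drop-out threshold of half the sessions and the rule "if a participant receives more than six EA/rTMS sessions, this will be considered a valid case to generate reliable data". If 20 sessions are planned, a patient with 7 to 9 is both a drop-out (fewer than 10) and a valid case. If the 12-session minimum is the denominator, half is six and the two rules nearly meet. This is a minor side point.

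**Conclusion.** The point holds in conditional form. For any patient analysed without a week-4 HAMD-24, the stated rule imputes no change at all, because nothing else can be carried forward. This is a rule the article fixes, and not a detail it leaves open.

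How much it matters depends on how many such patients there are, which is unknown, and on the test and the real baselines. On the planned means with r = 0.5, three per arm reduce power to about 0.42 (t test) or 0.87 (Mann-Whitney), and six per arm to 0.06 or 0.69. The lowest figures are not a forecast: they assume the t test, the cited study's severe baseline, and no week-4 rating for any of the planned 20% drop-outs. The direction of any bias from unequal loss cannot be predicted from the documents.

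**What to change.** 1. **Statistical analysis section.** Drop LOCF for HAMD-24. Analyse observed week-4 scores adjusted for baseline, or use multiple imputation under missing at random. Keep baseline carried forward as a sensitivity analysis at most.
2. **Drop-out criteria and Compliance and discontinuation sections.** State that stopping treatment or having too few sessions does not end follow-up. Seek the scheduled week-4 HAMD-24 from every randomised patient who has not withdrawn consent, and use it whatever the session count. The session threshold can be aligned in the same amendment.

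**Cost.** A protocol amendment and some effort to bring back patients who stopped. No visit is added: the week-4 rating is in Table 1, and WeChat and phone reminders are already planned. Some week-4 scores will reflect stopped or other treatment, which may dilute the difference between arms. If the patients brought back truly did not improve, measuring them restores no power (about 0.41 with three per arm at r = 0.5), but the result then rests on data. Recruitment began in October 2022, so the second change cannot reach patients already past week 4. The first change covers them, on the assumption that their missing scores are missing at random.
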